### Primary outcomes collected by the interactive voice response system

1. **Days of Heavy Drinking:** For this comparison, the AUDIT-C [25] heavy drinking question is asked, but is captured in the Interactive Voice Response System as the number of days when 4 or more drinks were consumed in the last week.

2. **Number of IPV events:** The 8 CTS2S [23] victimization questions are used to measure the incidence of IPV, and counts are collected for these questions each week via the interactive voice response system.

Our primary analytic method for the two group longitudinal comparisons will include implementing Hierarchical Generalized Linear Models (HGLM) to accommodate the clustering of the weekly repeated measures, as well as the nature of the outcome, which counts the number of heavy drinking days and the incidences of IPV per week. If the outcome measure displays a large proportion of zeroes, we will implement zero-inflated Poisson or zero-inflated Negative Binomial models, as appropriate with random effects. These models accommodate the clustering as well as the stack of zeroes present across the repeated assessments. [38] To assess the sensitivity of treatment effect estimates to missing data, we propose to fit the hierarchical regression models without accounting for informative missing data, and then compare these results with those from analyses that adjust for informative missing data. We will employ the pattern-mixture approach as applied to hierarchical regression models by Hedeker et al (1997). [39] Their methods assess whether important terms depend on certain missing data patterns, and provide equations to obtain unbiased estimates by averaging over the various missing data patterns.

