## Methods and design

### Setting, timeline, and general study design

This study is a longitudinal, randomized controlled trial, being conducted in two urban academic EDs staffed by emergency medicine faculty, residents, and nurse practitioners. These are the primary EDs and trauma units serving a 14-square mile area with mixed socioeconomic status and a population of over 200,000. Using a conservative prevalence range of 5-10% for risk of both IPV and problem drinking, we anticipated that recruitment from this medical venue would be adequate to achieve our target sample size based on the high patient volume (approximately 1,535 women subjects/year in the target age range). and the tendency for IPV victims and problem drinkers to receive their medical care from EDs The inclusion of two locations broadens our population and allows for greater generalizability.

Participants are randomized into one of three study groups using a 2:2:1 distribution: the intervention group (n = 240), the assessed control group (n = 240) and the no contact control group (n = 120). The assessed control group is interviewed at enrollment and at similar time points to the intervention group. The no contact control group is only assessed at 3-months, which enables us to determine the extent to which improvements over time in the intervention and assessed control groups maybe due to assessment reactivity.

This RCT began enrollment on January 18, 2011 and the target enrollment of 600 women was completed earlier than planned on November 6, 2013. Currently, we are in the middle of follow up data collection. Data collection will continue until approximately December 2014, the point at which all women in the intervention and assessed control group will have complete 12 month follow up measures.

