### Consent & randomization

Prior to consent, patients are informed that the enrollment process could take up to an hour to complete, whether or not they are discharged from the ED. Using the SPSS pseudorandom number generator [24], the study statistician created a block randomization scheme, in groups of 20, to determine study assignment. The project manager used the scheme to prepare two sets of opaque envelopes – one for each ED – that are indistinguishable from each other and thick enough so that their contents are not legible from the outside. All patients who give consent for participation are randomized by pulling the next sequential envelope. This process ensures that those who enroll participants are unaware of group assignment until after they are consented to be in the study; only the project manager and statistician are aware of the randomization scheme. For patients randomized to the intervention group, the RA presents a secondary consent for audio-recording of the motivational interview. Participants do not have to consent to audio-taping to participate in the study.

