Using the intent-to-treat analysis for all patients who complete enrollment as described above, we will rely on generalized linear modeling to examine baseline and 3-month responses, adjusting for any other covariates that are determined to be significant in the preliminary analyses. Through pair-wise comparisons, this analysis will also compare 3 month differences between the assessed control group and no contact control group to determine the impact of assessment on the outcomes. For the analyses of the impact of assessment bias, only participants with 3-month outcome data will be included analysis.

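### Allocation is blocked within each ED, but the stated models do not carry ED, and the secondary-outcome covariate rule cannot select it; prespecify ED as a fixed effect

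*Protocol article*

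**What the plan says.** **Allocation.** The trial is "being conducted in two urban academic EDs staffed by emergency medicine faculty, residents, and nurse practitioners". Under Setting, timeline, and general study design, "Participants are randomized into one of three study groups using a 2:2:1 distribution". Under Consent & randomization, "the study statistician created a block randomization scheme, in groups of 20, to determine study assignment". Then: "The project manager used the scheme to prepare two sets of opaque envelopes – one for each ED". Finally, "All patients who give consent for participation are randomized by pulling the next sequential envelope". The article does not use the word stratified, but separate blocked sequences drawn in order at each ED amount to stratification by ED.

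**Analysis.** Three places describe models, and none names ED.
- *Primary outcomes collected by the interactive voice response system:* "Hierarchical Generalized Linear Models (HGLM) to accommodate the clustering of the weekly repeated measures". Repeated weekly measures are the only clustering mentioned, and no covariate rule is given.
- *Analysis across all three groups:* a generalized linear model of baseline and 3-month responses, "adjusting for any other covariates that are determined to be significant in the preliminary analyses".
- *Secondary outcomes:* hierarchical linear models whose covariates are the variables on which the arms differ significantly at baseline.

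Main effects, moderator and mediator analyses lists the predictors to be explored (IPV severity, alcohol dependence, drug use, depression, PTSD, abuse history, partner drinking). ED is not among them.

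**The concern.** Blocking within ED removes the ED imbalance from the treatment contrast, so the true sampling variance of that contrast contains almost no between-ED component. A model without ED still counts between-ED variation as residual error. Its standard error is then larger than the true one, and the test rejects too seldom.

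The article does more than stay silent. It states two data-driven rules for choosing covariates, and the one for secondary outcomes works against a stratification factor: the better the blocking does its job, the less chance ED has of showing a difference between arms. The three-group rule leaves the entry of ED to the data. What is at stake is precision, mainly where arms are compared on level (the 3-month three-group comparison and the secondary outcomes).

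**Working it through.** **1. The plan's own figure.** Power for analyses gives 199 randomised per group for heavy drinking (alpha 0.025, at least 80% power, 30% attrition). I used n = 2(z_a + z_b)² × Var / effect², then divided by 0.7, with a slope difference of 0.109 − 0.046 = 0.063, autoregressive correlation 0.6, and SD rising from 0 at week 4 to 1.25 at week 12.
- Slope contrast over weeks 5–12: 146 completers, 208 randomised.
- Slope contrast over weeks 4–12: 148 randomised.
- Week-12 difference alone: 170 randomised.

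The article does not give the time points or attrition pattern, so 199 is neither confirmed nor shown wrong. This point does not rest on it. I use it only to set the number of completers: 199 × 0.7 ≈ 139 per group.

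**2. Can ED pass the secondary-outcome rule?** Blocks of 20 at 2:2:1 hold 8:8:4. I assume that whole blocks were placed in each ED's set, which the article implies but does not spell out. Imbalance between intervention and assessed control can then come only from one unfinished block per ED, at most 8 patients in each. The worst case has opposite signs in the two EDs:

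| Split between EDs | ED 1 (intervention vs control) | ED 2 | Chi-square (1 df) | p |
|---|---|---|---|---|
| about 50:50 | 128 vs 120 | 112 vs 120 | 480 × 1920² / (248 × 232 × 240 × 240) = 0.53 | 0.47 |
| 75:25 | 184 vs 176 | 56 vs 64 | 480 × 1920² / (360 × 120 × 240 × 240) = 0.71 | 0.40 |

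Here 1920 is the cross-product difference, for example 128 × 120 − 120 × 112. Among randomised patients ED cannot reach significance, so the rule cannot admit it.

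**3. Type I error without an ED term.** Simulation: 600 patients split 60:40 between EDs, 8:8:4 blocks within each ED, continuous outcome, two-sided alpha 0.025, 6000 runs. The Monte Carlo standard error is √(0.025 × 0.975 / 6000) ≈ 0.002.

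| ED difference (SD, assumed) | No ED term | With ED term |
|---|---|---|
| 0 | 0.023 | 0.023 |
| 0.3 | 0.025 | 0.026 |
| 0.5 | 0.023 | 0.026 |
| 1.0 | 0.013 | 0.027 |

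Error is never inflated by leaving ED out. The test is clearly conservative only near 1 SD.

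**4. Power.** The residual variance inflates by 1 + p(1 − p)d², where p is one ED's share and d the ED difference in SD. The true variance of the contrast stays as it was, so power = Φ(δ√(n/2) − z_a × √inflation). With n = 139, z_a = 2.241 and δ = 0.37 (chosen so that power with an ED term is 80.0%), δ√(n/2) = 3.085.

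| d | Inflation at 50:50 | Power at 50:50 | Power at 75:25 |
|---|---|---|---|
| 0.2 | 1.010 | 79.7% | 79.8% |
| 0.3 | 1.0225 | 79.3% | 79.5% |
| 0.5 | 1.0625 | 78.1% | 78.6% |
| 1.0 | 1.250 | 71.9% | 74.0% |

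Steps 3 and 4 use a simple linear comparison of means, so they are only indicative for the planned hierarchical count models.

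**The case against.** **The article never excludes ED.** The primary section names a class of model and gives no covariate list, and listing randomisation factors is commonly left to an SAP, which is not shown. This stands. A reader might infer that no model will include ED and that the analysis therefore contradicts the design; the article does not support that for the primary outcomes. What survives is narrower: the secondary-outcome rule is on the page and cannot select ED.

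**The two covariate rules differ.** The three-group rule does not say significant between arms. If it means related to outcome, ED could enter when it matters. This also stands. The objection there is only that the entry of a randomisation factor should not depend on the data.

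**The powered primary test is a rate of change.** An ED difference in level is a between-patient shift that patient random effects largely absorb. In a linear random-intercept model with complete data, adding an ED main effect leaves the group-by-time estimate unchanged. A reader might apply 1/√(1 − R²) to the primary tests, but that formula is for a simple comparison of means and does not carry over to a slope contrast in a random-effects count model.

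**There is slack.** The two-group comparison randomises 240 against a stated need of 199 (240/199 = 1.21), and the article claims 93.7% power for IPV at 199. That covers the smaller losses above. It does not extend to the comparisons with the no contact group, for which the article says the 240 is needed.

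**Case mix is not ignored.** A reader might say that ED differences in case mix stay unmodelled. Several clinical characteristics are to be examined as main effects and interactions, so that is too strong.

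**Conclusion.** The point holds as a free improvement, not as an error that threatens the trial's conclusions. Allocation is in effect stratified by ED. The secondary-outcome rule cannot admit ED, the three-group rule leaves it to the data, and the primary model does not name it.

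The consequence is a somewhat conservative test and a modest loss of precision. A reader might fear bias or false positives; within-ED blocking prevents the first, and the simulation shows none of the second. The loss is about 1 to 2 power points for EDs up to 0.5 SD apart and about 8 points at 1 SD. It falls mainly on comparisons of level, and the primary slope contrast may be little affected.

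This rests on three assumptions: whole blocks within each ED's envelope set, an ED difference somewhere in the assumed range of 0 to 1 SD (the article gives no figure), and a linear model as a stand-in for the planned ones.

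**What to change.** Prespecify ED (two levels) as a fixed effect in every two-group and three-group model, primary and secondary, whatever any significance test shows. State that ED is exempt from the covariate-selection rules in Analysis across all three groups and Secondary outcomes. If the SAP already does this, a sentence confirming it is enough.

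The cost is one term and one degree of freedom per model. ED is known for every patient from the envelope set used, so no new data are needed, and follow-up was still under way when the article was written.

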### Secondary outcomes

Secondary alcohol outcomes include changes in the full AUDIT [22] score and drinking data collected using a calendar based Timeline Followback [35] for the month (28 days) prior to the follow up interview. Secondary IPV outcomes include changes in the Composite Abuse Scale [36] and measures of the frequency and severity of IPV from the CTS2S.

Other health-related outcomes include: self-rated health, quality of life, sleep, and relationship satisfaction. For these secondary outcome measures collected at baseline, 3, 6, 9, and 12 months, Hierarchical Linear Models (HLM) will be implemented to compare the intervention and assessed control groups. Variables that show significant differences between the treatment groups at baseline will be included as covariates in the model.

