### Screening and subject recruitment

Data collection occurs approximately 10 hours per day, 6 days each week and ED providers are encouraged to make referrals of potentially-eligible patients during off hours. During data collection periods, Research Assistants (RAs) approach and attempt to screen all female patients in the ED using a psychosocial risk assessment (referred to as the Social Health Survey) that asks about IPV and risky drinking. Patients who indicated a risk for either IPV or risky drinking are asked to complete a formal assessment to determine study eligibility. The assessment includes the AUDIT [22] and CTS2S [23], is verbally administered by the RA to determine study eligibility of IPV and excessive drinking in the last 3 months – a score of 1 or more on the CTS2S and 4 or more on the AUDIT. For referrals outside of data collection hours and for women who are found to be potentially eligible but unable to stay in the ED, the Clinical Research Coordinator collects safe phone contact information to determine study eligibility and arranges an appointment for enrollment.

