### Structured women’s health interview

The women’s health interview is an extensive assessment, which includes a variety of validated measures for secondary outcomes, mediators and moderators (See Additional file 1: Table S1). Participants in the intervention and assessed control group are administered the interview at baseline, 3 months, 6 months, and 12 months. The no contact control participants only complete the interview at 3 months. All interviews are structured with close coded responses to validated questionnaires and take approximately 30 minutes to complete. Follow up interviews can be conducted over the phone or in person. RAs conducting follow up interviews are blinded to the participant’s group assignment during data collection. At the completion of all data collection, control group participants are offered an opportunity to receive the intervention, which is usually scheduled as a phone session by one of the motivational therapists.

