### Statistical analysis

#### Analysis across all three groups

With a goal of identifying the impact of assessment alone, the outcomes below can be analyzed across all three groups: the Brief Intervention Group (BIG), the Assessed Control Group (ACG) and the no contact control group (NCCG) using a intent-to-treat analysis that includes all participants who complete randomization and enrollment procedures and provide baseline and/or at least one follow up data collection point. Analysis across all groups including the no contact control group (NCCG) will include eligibility assessment data (baseline) and 3-month interview data collected on CTS2S and the AUDIT assessments.

Alcohol outcome measures are the frequency of heavy drinking (4 or more drinks/day for women) collected at baseline in person and by phone interview at 3 months using one item on the AUDIT [22], to calculate the frequency of 4 or more drinks. The full AUDIT score (0–40) [22] and additional drinking data are collected using a calendar-based Timeline Followback [35] for the month (28 days) prior to the interview.

IPV outcome measures include the frequency of IPV incidents (emotional, physical, and sexual) collected at baseline and by phone interview at 3 months using the CTS2S [23], scored 0–96. These data are on a likert scale, capturing a range of frequencies of occurrence in the previous three months. IPV Severity is calculated as the number of IPV incidents classified as severe in the preceding 3 months measured using specific items on the CTS2S [23]. IPV type and severity is also captured through the Composite Abuse Scale [36], scored 0–150.

All of the above measures are collected at baseline and 3, 6, and 12 months for the Intervention and Assessed Control Group and at 3 months only for the Non-Assessed Control Group. So any comparison across all 3 groups is limited to 3 month outcomes.

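### Covariates for the secondary and three-group models are to be picked by significance tests on trial data instead of being named in advance from the pre-randomisation AUDIT and CTS2S scores

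*Protocol article*

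**What the plan says.** Under *Secondary outcomes*, hierarchical linear models compare the intervention and assessed control groups, and the covariate rule is: "Variables that show significant differences between the treatment groups at baseline will be included as covariates in the model".

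Under *Analysis across all three groups*, a generalised linear model of baseline and 3-month responses is planned, "adjusting for any other covariates that are determined to be significant in the preliminary analyses". The text does not say whether significance there means a difference between groups or an association with outcome.

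Four other places bear on the point:

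- *Screening and subject recruitment*: the AUDIT and CTS2S are "verbally administered by the RA to determine study eligibility of IPV and excessive drinking in the last 3 months", which puts them before consent.
- *Analysis across all three groups*: that analysis "will include eligibility assessment data (baseline) and 3-month interview data collected on CTS2S and the AUDIT assessments", so the eligibility scores already count as baseline there.
- *Consent & randomization*: "All patients who give consent for participation are randomized by pulling the next sequential envelope". Enrolling staff learn the arm only after consent, and for intervention women "the RA presents a secondary consent for audio-recording of the motivational interview".
- *Structured women's health interview*: the interview is given at baseline to the intervention and assessed control groups, whereas "The no contact control participants only complete the interview at 3 months". Blinding is stated for the research assistants who do follow-up interviews. Nothing similar is said for baseline.

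**The concern.** In a randomised trial with sound allocation, any baseline difference between arms is due to chance, so testing it tells nothing about which variables predict outcome. A covariate earns its place by being prognostic. Selecting on imbalance brings in variables at random, leaves out most good predictors, and settles the model only after the data have been seen.

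This trial has an added weakness. Most of the candidate variables come from an interview given after allocation, by staff not stated to be blinded. If knowledge of the arm changed what was reported or recorded, the rule would favour the affected items, and adjusting for them would move the treatment estimate. At stake are the precision, reproducibility and credibility of the secondary comparisons and of the assessment-reactivity analysis.

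**Working it through.** **The plan's own figures.** None quantifies the covariate rule. The nearest is 199 per group for heavy drinking (*Power for analyses*). With a difference of 2/(52/12) = 0.4615 days/week, SD 1.25, two-sided alpha 0.025 and 80% power, n = 2(2.241 + 0.842)² × (1.25/0.4615)² ≈ 140. Dividing by 0.7 gives 200, which agrees with 199. That figure concerns a primary outcome, and the present point does not rest on it.

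**Chance selection.** For k independent variables tested at 0.05, P(at least one flagged) = 1 − 0.95^k and the expected number is 0.05k. The article gives neither k nor the threshold; both are assumed.

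- k = 10: 1 − 0.599 = 40%, expected 0.5
- k = 15: 1 − 0.463 = 54%, expected 0.75
- k = 20: 1 − 0.358 = 64%, expected 1.0

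**What the rule does to a prognostic variable.** The simulation used 168 women per arm (240 × 0.7, the plan's 30% attrition), one normal baseline variable, one normal outcome, an assumed effect of 0.3 SD, two-sided alpha 0.05 and 20,000 runs. The central correlation, 0.6, is borrowed from the plan's within-subject figure. The variable was selected in about 5% of runs.

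| Correlation | Power, selected if significant | Power, always adjusted | Type I error, selected | Type I error, always adjusted |
|---|---|---|---|---|
| 0.3 | 78.8% | 81.6% | 4.8% | 5.1% |
| 0.5 | 79.5% | 88.9% | 4.4% | 5.1% |
| 0.6 | 79.6% | 92.9% | 4.0% | 5.0% |
| 0.7 | 80.1% | 97.2% | 3.4% | 4.9% |

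With clean baseline data the rule is conservative, not liberal.

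**How much of that gap applies here.** The comparator in the table ignores baseline unless it is selected. The plan lists baseline among the measurement times of the hierarchical model, so some precision may be recovered. Relative variances at correlation 0.6 are 1 if baseline is ignored, 2(1 − 0.6) = 0.80 for change scores and 1 − 0.6² = 0.64 for covariate adjustment. At 0.5 the change score gains nothing, since 2(1 − 0.5) = 1. The table is therefore an upper limit on the loss when the outcome's own baseline is the variable concerned.

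**Order of allocation and interview.** Consented women are randomised at once by envelope. Two of the three arms then get a baseline interview. Staff cannot know whom to interview until the envelope is open, so the interview follows allocation. *Research assistants: training & supervision* gives the same staff both enrolment and the interview. The inference does not extend to the demographic form, which all participants complete at enrolment.

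**Conditional bias.** Same simulation, no true effect, correlation 0.6, with reporting in one arm shifted by an assumed amount:

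| Shift (SD) | Variable selected | Bias under rule (SD) | Type I error under rule | Type I error if this item is always adjusted for |
|---|---|---|---|---|
| 0.1 | 15% | −0.02 | 4.7% | 10.2% |
| 0.2 | 45% | −0.08 | 15% | 27% |
| 0.3 | 78% | −0.16 | 43% | 53% |

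Without adjustment, type I error stays at about 5%. The last column shows that naming a contaminated interview item in advance would not cure the problem. The covariate has to predate allocation.

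**The case against.** The case for the plan limits the point in several ways.

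- **Primary outcomes.** A reader might infer that the weekly telephone-survey models also lack baseline adjustment. The article is only silent there, and a covariate list is commonly left to the analysis plan. The stated rule belongs to the secondary outcomes.
- **Three-group analysis.** A reader might infer that the pre-randomisation scores go unused. They do not: the eligibility AUDIT and CTS2S are that model's baseline, and its rule concerns other covariates. Significance there may mean association with outcome, not imbalance. The choice is data-driven either way.
- **Other secondary outcomes.** Pre-randomisation values are shown only for the AUDIT and CTS2S. None is shown for the Composite Abuse Scale, Timeline Followback, self-rated health, quality of life, sleep or relationship satisfaction. For these the two scores can serve only as prognostic covariates.
- **Precision.** The full gap between 79.6% and 92.9% power should not be read as this trial's loss, because baseline may enter as a repeated response.
- **Type I error.** A reader might infer inflation. Chance imbalance in a true baseline variable produces none, and no part of the article shows that allocation changed baseline reporting. At a 0.1 SD shift the error is still 4.7%.

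All of this stands. None of it defends the written selection rules, which are explicit statements and not gaps left for another document.

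**Conclusion.** The point holds for the two-arm secondary-outcome models and, in weaker form, for the three-group model. Both let the trial data choose the covariates. The secondary rule uses a criterion that flags about 5% of variables by chance, with a 40% to 64% chance of at least one flag if 10 to 20 independent variables are tested at 0.05.

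If baseline reporting was unaffected by arm, the cost is an unpredictable model and some lost precision, of a size the article does not allow one to fix. Bias arises only if knowledge of the arm shifted reporting at the baseline interview. The design leaves that open but does not show it. The order of allocation and interview is inferred from three sections, not stated in one sentence, though the no-contact arm makes it necessary. The point should be corrected before analysis; it does not undermine the trial.

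**What to change.** Delete the baseline-significance rule under *Secondary outcomes* and the preliminary-significance rule under *Analysis across all three groups*. In their place, name the covariates:

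- drinking outcomes: the pre-randomisation AUDIT score, or its heavy-drinking item;
- violence outcomes: the pre-randomisation CTS2S score;
- health-related outcomes: both scores as prognostic covariates. The outcome's own baseline may enter the hierarchical model as a repeated response, with a note that it was measured after allocation.

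Keep the eligibility AUDIT and CTS2S baseline already in the three-group model. Do not pick post-allocation interview items as adjusters because they look imbalanced; they can remain as the planned moderators. State how baseline enters the hierarchical models.

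The cost is wording only. Both scores were needed to establish eligibility, so they should be held for every randomised woman, and the article reports follow-up as still running.
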